**PROPOSED STARTING DATE: 1 January 2009**

**DURATION (MONTHS): 48 months**

**TOTAL BUDGET REQUESTED: US$ 1,473,510**

**TOTAL BUDGET SPEND IN NORTHERN INSTITUTIONS* US$**

**INSTITUTION WHERE GRANT TO BE HELD: London School of Hygiene & Tropical Medicine**

**SITE(S) OF RESEARCH (COUNTRIES, LOCATIONS, INSTITUTIONS):**

Kintampo Health Research Centre’s field research area in Ghana

**AIMS OF THE ACT CONSORTIUM THIS PROJECT ADDRESSES*- delete those what do not apply**

1. Improving drug targeting.

**Protocol version 2; date 1 December 2008**

**d. Stage 2 Component A: effects of restricted use of ACTs based on RDT results: a randomised controlled trial**

**d.1 Research questions** :

***Primary:***

What is the effect of restricting ACT to RDT positive cases of malaria compared to offering ACT on the basis of clinical judgement on the incidence of malaria in children < 4 years of age?

***Secondary:***

1. What is the effect of restricting ACT to RDT positive cases of malaria on the incidence of severe anaemia?
2. What is the effect of restricting ACT to RDT positive cases of malaria on the incidence of other severe febrile diseases?
3. What is the effect of RDT on the use of antibiotics for treating febrile illness?
4. Is restricting ACT to RDT positive cases of malaria cost-effective?
5. What is the effect of RDT on the community perception of the quality of care and the treatment seeking behaviour in particular for febrile illness in young children?

**d.2. Study design**: Cluster randomised two arm trial

**Study area**: The study will be conducted in Kintampo Health Research Centre field research area in Ghana. There are 36 government health facilities in the seven districts. The catchment population of these health facilities range from 10,000 to 85,000.

**d.3. Outcomes**

***Primary****:* Incidence of malaria (fever + any level of parasite density) in < 48 month-old children

***Secondary outcomes*:**

1. incidence of severe anaemia (Hb <8 g/dl) in < 48 month old children
2. incidence of any severe febrile illness in < 48 month old children
3. mean number of sick days in < 48 month old children
4. probability of using antibiotics for treating febrile illness in <48 month old children

**d.4. Study groups and enrolment of study children**:

The unit of randomisation will be health centres (HC). HCs will be randomly assigned either to the RDT+ACT group (ACT offered to RDT positive cases only) or to the clinical judgement+ACT group (ACT offered to all suspected cases of malaria by clinical judgement). Households within 10km radius of the HCs will be enumerated and one hundred <24 month old children from these households will be enrolled after obtaining informed consent from caretakers in each HC. At enrolment a photoID card of study children will be given to the caretakers and they will be advised to bring the photoID card when ever they bring the study children to the health facilities for treatment. The intervention and follow up will be continued for 24 months from enrolment.

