**d..6. Interventions**:

The study objectives will be explained to all staff involved in managing febrile cases in the study health centres (HCs). Staff in the RDT+ACT HCs will be trained in (1) using RDTs, (2) prescribing ACT to RDT positive cases only, and (3) further investigation of RDT negative cases for other infectious diseases. Staff in the clinical judgement + ACT HCs will undergo refresher courses in the clinical diagnosis of malaria and other infectious diseases with similar signs and symptoms, and management of malaria, and they will be advised to continue the current policy of offering ACT to all suspected cases of malaria. HC staff will identify study children using the PhotoID cards. Study children attending RDT+ACT HCs with a febrile illness will be tested with an RDT to confirm malaria and treated with ACT only if they have a positive test for malaria parasite. However if there are signs suggestive of other co-morbidities they will be treated with appropriate medicines in addition to AS+AQ. Children attending clinical judgement + ACT HCs with a febrile illness will be treated with ACT on the basis of the clinical judgement. Children and adults who are not enrolled in the study attending HCs in both arms with a febrile illness will be treated according to the current treatment guidelines ie.based on clinical judgement and using microscopy when feasible. The intervention will be continued for 24 months from the time of enrolment of study children.

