**d.8. Sample size**:

***Effect of RDT+ACT on in the incidence of malaria***: To assess the effect of RDT+ACT on the incidence of malaria children under 48 months of age would require 30 clusters (15 per arm) and 200 PYAR per cluster on the basis of the following assumptions: (1) Incidence of malaria in the clinical judgement + ACT group would be 0.8 episode/ 1 PYAR (the rate observed in the IPTi group of <24 month old children in Navrongo, Ghana6); (2) The study would have 80% power at 95% significance level to detect a 20% difference in the incidence of malaria between the two comparison groups and this level of difference is deemed to be the non-inferiority margin of public health importance; (3) the coefficient of variation in the incidence of malaria between clusters will be 0.18

***Effect of RDT+ACT on in the incidence of severe anaemia***: Incidence of severe anaemia in the RDT + ACT group is expected to be 37/1000 PYAR (the rate observed in the 16-24 month old children who received placebo in Navrongo, Ghana6). The study would have 80% power at 95% significance level to detect a 36% reduction in the incidence of severe anaemia between the two comparison groups.

***Effect of RDT + ACT on febril children requiring referral:*** Actively following up 2000 episodes of febrile illness seen at 20 study HCs will have 85% power to detect 50% difference between the two arms assuming 1) risk of referral in the RDT + ACT group would 0.05; (2) the coefficient of variation in the risk of referral 0.1

Although mortality will be measured the study does not have adequate power to detect any difference between the groups.

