**d..9 Effect of other malaria control interventions**

Coverage with other malaria control interventions, such as insecticide treated nets (ITNs) will be assessed during the prevalence surveys. Conclusions on the efficacy of the alternative case management strategies will be generalisable at the coverage levels of other interventions present in the study area. Antimalarial and other drugs are available in several formal and informal sector outlets and this may affect the adherence to the treatment regime of the study participants. Attempts will be made to maximise adherence to study protocol by participants through behaviour change communication strategies. At the monthly active follow up visits of study children the history of treatment received from any other health care provider other than the designated HCs will be documented and this information will be used to assess the extent of contamination of the study outcomes.

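### The d.4 enrolment rule lets a child who lives nearer to an opposite-arm health centre be enrolled; any resulting crossover would pull the malaria rate ratio towards 1, against a 20% non-inferiority margin

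*Protocol*

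**What the plan says.** Section d.4 randomises health centres and sets one geographic condition for enrolment: "Households within 10km radius of the HCs will be enumerated and one hundred <24 month old children from these households will be enrolled". It gives no nearest-centre rule, no minimum spacing between study HCs, and no rule for a household that lies inside two circles.

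Section d.6 describes care by the centre attended. For one arm: "Study children attending RDT+ACT HCs with a febrile illness will be tested with an RDT to confirm malaria". For the other: "Children attending clinical judgement + ACT HCs with a febrile illness will be treated with ACT on the basis of the clinical judgement". Of the photo card it says "HC staff will identify study children using the PhotoID cards"; nothing says that the card shows the arm or the HC of enrolment.

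On the number of centres, the study area paragraph in d.2 says "There are 36 government health facilities in the seven districts", and section d.8 says the primary outcome "would require 30 clusters (15 per arm) and 200 PYAR per cluster". Section e.4 counts 28 trial centres.

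Section d.9 acknowledges contamination. It plans behaviour change communication to improve adherence, refers to designated HCs, and has monthly visits record treatment received from other providers, adding that "this information will be used to assess the extent of contamination of the study outcomes".

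**The concern.** In a cluster trial the contrast between arms depends on children receiving the strategy of the cluster in which they are counted. A bare radius does not secure this. Two study HCs less than 20 km apart have overlapping 10 km circles. A household in the overlap qualifies for both clusters, and half of the overlap is nearer to the other HC. If the two HCs are in opposite arms, a caretaker who simply uses the closer one takes the child to the wrong arm.

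Crossover in both directions makes the arms alike. That matters more than usual here, because d.8 calls the 20% difference a non-inferiority margin. Dilution then favours the conclusion that restricting ACT does no harm. The comparisons of severe anaemia and antibiotic use would be diluted in the same way. The sample size in d.8 makes no allowance for this.

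**Working it through.** **1. The plan's own figure.** Inputs from d.8: control rate 0.8 per person-year, 20% difference, 200 person-years per cluster, between-cluster coefficient of variation k = 0.18, 80% power, 5% significance (taken as two-sided; d.8 does not say). The standard cluster-rate formula is

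c = t + (1.96 + 0.84)² × [(r0 + r1)/y + k²(r0² + r1²)] / (r0 − r1)²

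With r0 = 0.80 and r1 = 0.64 (a 20% reduction), the bracket is 0.0072 + 0.0340 = 0.0412, and the second term is 7.85 × 0.0412 / 0.0256 = 12.6. Adding t = 1 gives 13.6 (14 per arm); adding t = 2 gives 14.6 (15 per arm). The stated 15 per arm is reproduced with t = 2, with no allowance for crossover.

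**2. How many centres are in the trial.** 30 of 36 (d.8) is 83%; 28 of 36 (e.4) is 78%. There is little room to choose only widely separated centres, and a child's alternative government facility will often be another study HC.

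**3. Geometry (distances assumed; the protocol gives none).** For two circles of radius r = 10 km with centres d km apart, the shared area is 2r²·arccos(d/2r) − (d/2)·√(4r² − d²), out of πr² = 314.2 km². By symmetry half of the shared area is nearer to the other HC. If half of neighbouring pairs are in opposite arms, halve again.

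| d (km) | Shared area (km²) | Share of circle | Nearer to other HC | Nearer to an opposite-arm HC |
|---|---|---|---|---|
| 15 | 45.3 | 14% | 7% | 4% |
| 10 | 122.8 | 39% | 20% | 10% |
| 5 | 215.2 | 69% | 34% | 17% |

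Reading the last column as crossover also assumes evenly spread households, one neighbouring HC, and that every child nearer to the other HC makes all febrile visits there.

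**4. Dilution.** With a share c of care crossing in each arm and a true ratio of 1.20, the observed ratio is [(1 − c)·1.2 + c] / [(1 − c) + 1.2c].

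- c = 0.05: 1.190/1.010 = 1.18
- c = 0.10: 1.180/1.020 = 1.16
- c = 0.17: 1.166/1.034 = 1.13

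**5. Effect on a non-inferiority conclusion.** Take the true ratio to be exactly at the margin of 1.20, a one-sided 2.5% test on the log ratio, and 15 clusters per arm with t = 1. The diluted rates are λ0 and λ1 (0.8 times the denominators and numerators in step 4). The standard error is √{[1/(200λ0) + 1/(200λ1) + 2 × 0.18²]/14}, about 0.074 throughout. The chance of wrongly declaring non-inferiority is Φ{[ln 1.2 − ln(observed ratio)]/0.074 − 1.96}.

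| Crossover in each arm | ln 1.2 − ln(observed ratio) | Chance of false non-inferiority |
|---|---|---|
| 0% | 0 | 2.5% |
| 5% | 0.0183 | 4.3% |
| 10% | 0.0366 | 7.2% |
| 17% | 0.0622 | 13% |

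**The case against.** The strongest reply has four parts.

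- **The protocol is not silent on contamination.** A reader might infer that nothing is done to prevent it. That is wrong: d.9 plans behaviour change communication, which may reduce crossover, and its monthly record will measure it. What remains is that persuasion and measurement come after enrolment and do not keep out a child who lives nearer to an opposite-arm HC.
- **Children have designated centres.** The wording in d.6 can be read as describing children at their own HC. The protocol does not address a study child who turns up at a centre of the other arm. That such a child is managed by the arm attended is the natural reading, but it is an inference and not a stated rule.
- **Crossover is not shown.** A reader might infer that children will cross over and that the excess will be diluted. The documents give no distances between HCs and no attendance data, so they support only that it could happen. If study HCs are all at least 20 km apart, no circles overlap.
- **The 4% to 17% range rests on stacked assumptions.** For a given pair of HCs, full attendance at the nearer centre is close to a ceiling. More than one close neighbour could push the figure up. At the lower end the effect is modest: 1.18 in place of 1.20.

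All four limit the strength of the point. None supplies the missing rule for households near two study HCs.

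**Conclusion.** The point holds as a gap in a sampling rule that the protocol itself fixes. As written, d.4 permits enrolment of children who live nearer to an opposite-arm HC, and nothing later in the protocol removes them. Overlap is plausible because 28 to 30 of 36 facilities are in the trial, but it is undocumented. The direction of the bias is clear: symmetric crossover pulls the ratio towards 1 and favours non-inferiority at the 20% margin. Its size is unknown. The ratios of 1.18, 1.16 and 1.13, and the false non-inferiority chances of about 4%, 7% and 13%, are illustrations under the assumed distances and attendance, not estimates for this trial. This is a worthwhile, inexpensive improvement to the design; it does not show that the trial's result will be biased.

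**What to change.** In d.4, add that each enumerated household is assigned to its nearest study HC before allocation is known, and that each HC's 100 children are drawn only from households assigned to it.

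The rule works on the enumeration list already planned and adds no children, visits or staff. The timetable places enumeration and the training of HC staff in the same quarter (Q5), so the assignment has to be completed before arm-specific training reveals the allocation. If the HCs prove to be well separated, the rule changes almost nothing.

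There are two costs. Enrolled children will live somewhat closer to their HC, so remote households are less represented. Each HC's sampling area may also shrink. The smallest catchment in d.2 is 10,000 people, but the protocol does not give the share under 24 months, so it is an assumption, to be checked on the enumeration list, that 100 eligible children remain in every cluster. The rule does not stop a caretaker from choosing a more distant HC; the communication and monthly recording in d.9 remain needed for that.

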**d..5. Inclusion/Exclusion criteria**

Children having chronic illnesses such as severe malnutrition and heart disease will be excluded from the study.

**d..6. Interventions**:

The study objectives will be explained to all staff involved in managing febrile cases in the study health centres (HCs). Staff in the RDT+ACT HCs will be trained in (1) using RDTs, (2) prescribing ACT to RDT positive cases only, and (3) further investigation of RDT negative cases for other infectious diseases. Staff in the clinical judgement + ACT HCs will undergo refresher courses in the clinical diagnosis of malaria and other infectious diseases with similar signs and symptoms, and management of malaria, and they will be advised to continue the current policy of offering ACT to all suspected cases of malaria. HC staff will identify study children using the PhotoID cards. Study children attending RDT+ACT HCs with a febrile illness will be tested with an RDT to confirm malaria and treated with ACT only if they have a positive test for malaria parasite. However if there are signs suggestive of other co-morbidities they will be treated with appropriate medicines in addition to AS+AQ. Children attending clinical judgement + ACT HCs with a febrile illness will be treated with ACT on the basis of the clinical judgement. Children and adults who are not enrolled in the study attending HCs in both arms with a febrile illness will be treated according to the current treatment guidelines ie.based on clinical judgement and using microscopy when feasible. The intervention will be continued for 24 months from the time of enrolment of study children.

**d.7. Measuring outcomes**:

***Incidence of malaria:***

Passive surveillance: All study children presenting with a history of fever to the study HCs will be identified using photoID cards and assessed with a morbidity questionnaire and a blood sample (blood slide and filter paper) will be collected to assess malaria parasite. Since the decision to offer an antimalarial drug will be based on RDT results or clinical judgment the blood slides will have limited use for treatment decision making. However, the blood slides will be at Kintampo Health Research Centre and the results will be reported to the health centres.

Active surveillance: Study children will be visited once a month at home and a morbidity questionnaire and blood samples (blood slide and filter paper) will be collected to assess malaria parasite if a child has a history of fever in the past 48 hours. Those who have a positive blood slide will be treated with ACT.

Both passive and active surveillance of malaria will be continued for 24 months from enrolment.

***Incidence of severe anaemia***:. All study children attending study HCs will be clinically assessed using a morbidity questionnaire and the Hb will be tested using a haemacue machine if anaemia is suspected by clinical examination. Children with Hb <11 gms/dl will be given appropriate treatment according to the national treatment protocol.

***Incidence of severe febrile illness and mean number of sick days:*** These outcomes will be measured in 100 episodes of febrile illness (50 in the wet and 50 in the dry season) in 10 randomly selected study HCs per arm. These children will be actively followed up on day 1,2,3 and 7 post treatment to assess the progress of their illness. If the illness has resolved by day 7, the number days the child was ill will be collected from the caretaker’s report. If the illness has not resolve by day 7 the child will be referred to the hospital and the number of days of illness will be collected from hospital discharge summary. The mean number of days of illness and the proportion of children requiring reference will be compared between the two groups.

***Use of antibiotics:*** The use of antibiotics will be monitored through the morbidity questionnaire completed during each visit to the study PHCs by study children.

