**d.10 Summary of data and biological sample collection per child**

| Procedures | enrolment | Unscheduled visits to PHCs | Monthly Scheduled home visits |
| --- | --- | --- | --- |
| Consent | √ |  |  |
| PhotoID | √ |  |  |
| Baseline socio-demographic, contextual factors CRF | √ |  |  |
| RDT testing |  | √ |  |
| ACT based on RDT result |  | √ (only In RDT+ACT PHCs) |  |
| Morbidity CRF |  | √ | √ (if history of fever in past 2 days) |
| Blood slide and filter paper sample |  | √ | √ (if history of fever in past 2 days) |
| Hb (Haemacue) |  | √ | √ (if history of fever in past 2 days) |

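### Sections d.7 and d.10 give different rules for measuring Hb, and the d.7 rule leaves severe anaemia open to differential detection in an open, cluster-randomised trial

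*Protocol*

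**What the plan says.** The first secondary outcome in section d.3 is "incidence of severe anaemia (Hb <8 g/dl) in < 48 month old children". Two places say when Hb is measured.

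- **Section d.7, severe anaemia paragraph.** Study children attending the health centres are examined clinically, and "the Hb will be tested using a haemacue machine if anaemia is suspected by clinical examination". The active-surveillance paragraph of the same section says that at home visits "a morbidity questionnaire and blood samples (blood slide and filter paper) will be collected to assess malaria parasite if a child has a history of" recent fever. It does not mention Hb.
- **Table d.10.** The Hb row reads "Hb (Haemacue) | | √ | √ (if history of fever in past 2 days". Hb is ticked at unscheduled visits with no condition, and at monthly home visits subject to recent fever.

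On who knows the allocation, section d.4 states "The unit of randomisation will be health centres (HC", and section d.6 states "The study objectives will be explained to all staff involved in managing febrile cases in the study health centres (HCs". Section d.6 trains RDT+ACT staff in, among other things, "further investigation of RDT negative cases for other infectious diseases". Comparator staff receive refresher courses in the clinical diagnosis of malaria and of other infections that resemble it. No masking of staff or of the decision to test Hb is described.

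**The concern.** There are two problems, and the second depends on how the first is resolved.

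First, the numerator of the outcome is not fixed. A team following d.7 counts only cases found on suspicion at a health centre. A team following d.10 also counts cases found at febrile home visits, and perhaps cases found at health-centre visits where nobody suspected anaemia. The two teams would report different incidences from the same children.

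Second, under the d.7 rule a case is recorded only if a staff member chooses to test. The staff work in a centre allocated to one arm, know the study objectives and have had arm-specific training. If the threshold for suspecting anaemia differs between arms, recorded incidence differs even when true incidence does not. The comparison would then mix an effect on anaemia with an effect on testing.

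The outcome answers the first secondary question, has its own power statement in d.8, and is listed among the primary outcomes of the cost-effectiveness component (section e.3).

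**Working it through.** **Side-by-side reading**

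| | d.7 text | d.10 table |
|---|---|---|
| Health-centre visit | Hb if anaemia is suspected | Hb ticked, no condition |
| Monthly home visit | Hb not mentioned | Hb if fever in past 2 days |

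The home-visit row cannot be reconciled as it stands: d.10 gives an explicit condition of its own, and d.7 has no counterpart. The health-centre row is weaker evidence, because other bare ticks in d.10 also omit conditions that the text supplies.

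**Inputs**

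- Rate λ = 0.037 per PYAR: d.8, "Incidence of severe anaemia in the RDT + ACT group is expected to be 37/1000 PYAR".
- Clusters c = 15 per arm, with y = 200 PYAR each: d.8, malaria sample size.
- Planned difference 36%, that is, a ratio of 0.64, with 80% power (d.8). The 95% significance level is taken as two-sided 0.05.
- Between-cluster CV k: none is given for severe anaemia. The malaria value of 0.18 is borrowed, and 0 to 0.25 is examined.

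**Formula.** The Hayes–Bennett formula for unmatched cluster rates, solved for power:

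Power = Φ( √[(c − 1)(λ₀ − λ₁)² / V] − 1.96 ), with V = (λ₀ + λ₁)/y + k²(λ₀² + λ₁²).

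**Step 1: the plan's own figure.** λ₀ = 0.037 and λ₁ = 0.64 × 0.037 = 0.02368.

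- k = 0: V = 0.06068/200 = 0.0003034; √(14 × 0.01332²/V) = 2.86; power 81.6%.
- k = 0.10: power 79.2%.
- k = 0.18: V = 0.000366; root 2.61; power 74.1%.

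The stated 80% is reproduced for a CV of about 0 to 0.10.

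**Step 2: unequal detection, no true effect.** The true rate is 0.037 in both arms. The recorded rate is 0.037 times the share of cases detected. The detection shares are assumptions; the documents give none.

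- *70% versus 60%.* Recorded rates are 0.0259 and 0.0222; ratio 0.70/0.60 = 1.17, inverse 0.86, an apparent 14% difference on the reduction scale. With k = 0.18, V = 0.000278; √(14 × 0.0037²/V) = 0.83; Φ(0.83 − 1.96) = 12.9%.
- *65% versus 50%.* Recorded rates are 0.02405 and 0.0185; ratio 0.65/0.50 = 1.30, inverse 0.77, an apparent 23% difference. V = 0.000243; root 1.33; Φ(1.33 − 1.96) = 26.5%.

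At k = 0 these chances are 14.3% and 29.6%; at k = 0.25 they are 11.9% and 24.3%. The nominal value is 2.5% per direction.

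**Step 3: comparison with the target.** A 36% reduction is a ratio of 0.64, or 1.56 inverted. On the log scale, ln 1.17/ln 1.56 is about 35% of the target and ln 1.30/ln 1.56 about 59%.

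**Step 4: equal under-detection.** If the same share is missed in both arms there is no bias, but power falls. At k = 0.18 it goes from 74% to 66% with 80% detected, and to 55% with 60% detected.

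**The case against.** **The table is only a summary.** The RDT and blood-slide rows also carry bare ticks at unscheduled visits, although d.6 confines RDT to febrile children in one arm and d.7 confines slides to children with a history of fever. This stands for the health-centre column: a reader might infer that d.10 requires Hb at every unscheduled visit, and the tick does not firmly say so. It does not explain the home-visit cell.

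**The direction of bias is not shown.** A reader might infer that RDT+ACT staff will test more, because they are trained to investigate RDT-negative children further. That training concerns other infectious diseases and does not mention anaemia or Hb, and comparator staff also receive a diagnostic refresher. Detection could be higher in either arm. This stands. What remains is that nothing protects equal testing.

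**The size is hypothetical.** A reader might set 1.30 beside 36% and conclude that detection bias could match the target effect. The two figures are on different scales. As reductions the illustrations are 14% and 23%, well short of 36%, and the detection shares are assumed. The inflated chance of a false finding remains if shares of that order occur.

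**The planning rate.** It is tempting to say that 37/1000 PYAR will not be reached when tests are done only on suspicion. The protocol does not say how anaemia was ascertained in the cited trial, so that cannot be judged.

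**Staff awareness is an inference.** The protocol does not use the word unblinded, nor say who performs the examination. With whole centres allocated, objectives explained and training by arm, the inference is firm for health-centre staff. Home visits should not be called arm-neutral either: no masking of visitors is described, and the fever trigger may itself be affected by the intervention.

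**Conclusion.** The point holds as a should-fix. Sections d.7 and d.10 conflict on where Hb is measured, and probably on what triggers it. If d.7 is followed, severe anaemia is recorded at the discretion of staff who know their arm.

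The discrepancy is read directly from the text. The size of any bias is not: it rests on assumed detection shares, a borrowed CV of 0.18 and the protocol's rate of 0.037. On those terms, detection gaps of 10 to 15 percentage points give false ratios of 1.17 to 1.30 and roughly a 13% to 27% chance of a significant result in that direction, in place of 2.5%. The documents support neither a direction nor a bias as large as the 36% target. The outcome is secondary, and the Hb rule does not enter the definition of the primary malaria outcome.

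**What to change.** Reconcile d.7 and d.10 to one rule for ascertaining the outcome, stated in both places, identical in the two arms and independent of staff suspicion. One option is Hb at the febrile health-centre visits and febrile home visits, where blood is already taken for the slide and d.10 already lists Hb. Then:

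- define severe anaemia (Hb <8 g/dl) on those measurements only;
- record Hb tests done on clinical suspicion separately, so that they do not enter the main comparison;
- report the number of Hb tests per PYAR by arm, so that readers can judge whether testing was equal.

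The cost is a short amendment and more HemoCue tests than the d.7 wording implies. Some dependence on behaviour remains: the outcome would still rest on attendance and reported fever, and treatment seeking is itself one of the study's secondary questions. The treatment of children found to have low Hb is a separate matter that this change does not prescribe.

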**Outcomes**

Mean number of sick days in children under 48 months of age

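### Sick days come from the caretaker if the illness resolves by day 7 but from a hospital discharge summary if it does not, so the longest durations may be under-recorded or missing

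*Protocol*

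**What the plan says.** Protocol section d.3 lists among the secondary outcomes the "mean number of sick days in < 48 month old children". Section e.3 uses it again as a secondary outcome of the cost-effectiveness component: "Mean number of sick days in children under 48 months of age".

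Section d.7 measures it in a sample of "100 episodes of febrile illness (50 in the wet and 50 in the dry season) in 10 randomly selected study HCs per arm". Section d.8 speaks of 2,000 episodes at 20 health centres, so this means 100 episodes per centre and 1,000 per arm. The children are "actively followed up on day 1,2,3 and 7 post treatment to assess the progress of their illness", and no later contact is given for this sample.

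The data source then depends on the day-7 finding:

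- Resolved: "the number days the child was ill will be collected from the caretaker".
- Not resolved: "If the illness has not resolve by day 7 the child will be referred to the hospital". The source of the duration changes with that step, since "the number of days of illness will be collected from hospital discharge summary".

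Durations from both sources are averaged and the two arms compared. As a separate comparison, "the proportion of children requiring reference will be compared between the two groups".

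**The concern.** One outcome has two instruments, and the value of the outcome decides which is used. A caretaker can report the whole illness from onset to recovery. A discharge summary describes a hospital stay. It may or may not state when the illness began, and it cannot show illness that continues after discharge. If a referred child does not attend, or attends and is not admitted, there is no summary, and the protocol gives no other source.

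The values at risk are the longest illnesses. The trial asks whether restricting ACT to RDT-positive children is acceptable, and the protocol itself plans for the share of unresolved episodes to differ by arm. Under-recording would then remove more illness time from the arm with more unresolved children, which tends towards reassurance.

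Existing procedures do not fill the gap. Under section d.10, the morbidity form at the monthly home visit is completed only if there was fever in the past 2 days. A child who has recovered by that visit leaves no recorded end date, and no later analysis can recover a date that nobody collected.

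**Working it through.** **Inputs from the protocol.** 10 centres per arm and 100 episodes per centre (d.7 with d.8); referral risk 0.05 in the RDT+ACT arm, a 50% difference, coefficient of variation 0.1 and stated power 85% (d.8).

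**Inputs assumed.** The protocol gives no illness durations. I take a mean of b = 3.5 days for resolved and L = 12 days for unresolved episodes, the same in both arms, and vary them below. I read the 50% difference as 0.05 against 0.025.

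**1. The plan's own figure.** The only power stated for this sample is for referral. With the cluster formula for proportions:

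- Variance term: 0.05×0.95/100 + 0.025×0.975/100 + 0.1²×(0.05² + 0.025²) = 0.000475 + 0.00024375 + 0.00003125 = 0.00075.
- With one cluster per arm deducted: √(9 × 0.025² / 0.00075) = √7.5 = 2.739.
- Power: Φ(2.739 − 1.645) = 86.3% one-sided; Φ(2.739 − 1.960) = 78.2% two-sided.

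The stated 85% is thus approximately reproduced on a one-sided reading. This supports 0.05 against 0.025 as a reasonable reading; 0.05 against 0.075 gives 56.4% and 0.05 against 0.10 gives 97.2% (both two-sided). Nothing below depends on the power figure. No power is stated for mean sick days.

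**2. Episodes affected.** 1,000 × 0.05 = 50 and 1,000 × 0.025 = 25, about 75 of 2,000.

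**3. Effect on the difference in means.** Arm mean = (1 − p)×b + p×u, where p is the share unresolved and u the duration recorded for those children. The difference, RDT+ACT minus clinical judgement, is 0.025 × (u − b).

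| Recorded for unresolved children | RDT+ACT | Clinical judgement | Difference |
|---|---|---|---|
| True duration, 12 days | 3.925 | 3.7125 | +0.21 |
| 7 days plus a 3-day stay | 3.825 | 3.6625 | +0.16 |
| 7 days only (known from the day-7 visit) | 3.675 | 3.5875 | +0.09 |
| Dropped, no value | 3.5 | 3.5 | 0 |

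**4. Range over the assumed durations.** With b of 3 or 4 days and L of 10, 14 or 21 days:

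- True difference: 0.15 to 0.45 day.
- Half of the referred children without a value: 0.08 to 0.23 day, about half the true difference.
- Only the days after day 7 recorded: −0.03 to 0.28 day.
- All referred children dropped: 0.

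**The case against.** The strongest reply is that the protocol asks the summary for days of illness, not length of stay. A summary may give the onset, and the day-7 visit already shows at least 7 days of illness. Only about 2.5 to 5% of episodes are affected on the planning risks, in a secondary outcome with no stated power. Handling of missing values can be left to the analysis plan. All of this limits the size of the problem. It does not remove it: the protocol does not say which days count, names no source when there is no summary, and an analysis plan can impute or censor a duration but cannot supply it.

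A reader might infer three stronger things that the document does not support.

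- *The arm difference disappears.* Recording a bare 3-day stay would give 3.475 against 3.4875, a difference of −0.01. But that credits children seen ill at day 7 with less illness than the 3.5 days assumed for those who recovered. Zero is reached only in extreme cases, such as short illnesses with only in-hospital days counted, or every referred child lost. The illustration also gives both arms the same mean among resolved episodes; a real difference there would be untouched.
- *The referral comparison is biased too.* For the day-7 rule, the need for referral is established at the day-7 visit, before any hospital document exists. A child who never reaches hospital still required it.
- *Children admitted before day 7 fall outside the rules.* The rule turns on whether the illness has resolved by day 7, not on where the child is. A child admitted early and well by day 7 has a caretaker report; one still ill falls under the second branch. The sick-day value for a child who dies is not stated, but that can be left to the analysis plan.

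**Conclusion.** The point stands as a measurement weakness in one secondary outcome, also used in the cost-effectiveness component. Durations beyond day 7 may be under-recorded or missing, which can bias the difference in mean sick days, usually towards zero. In the main illustration a true +0.21 day becomes +0.16, +0.09 or 0.

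This rests on assumed durations, on a referred share that differs by arm as section d.8 plans, and on recording that fails equally often in both arms. If the shares were equal, most of the error would cancel. If the 50% difference were meant as 0.05 against 0.075 or 0.10, the number of affected episodes would change, to 50 against 75 or 50 against 100, but not the mechanism. The primary outcome and the referral proportion are unaffected. Minor severity, and a cheap improvement.

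**What to change.** In section d.7:

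- Define illness days once, for all sampled episodes, as onset to resolution by caretaker report.
- For a child unresolved at day 7, record the resolution date at the next scheduled monthly home visit, or at a later one if the child is still ill, whether or not there is fever at that visit.
- Keep the discharge summary as a supplementary source.
- Do not drop a child for lack of a summary. At minimum, treat the duration as censored at day 7 or at the last later contact.

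The referral rule and the severe-illness outcome stay as they are.

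The cost is a few sentences in the protocol and one item on the monthly form, for about 75 children on the planning risks (125 or 150 on the other readings of the 50% difference). The home visits are already scheduled. The drawback is longer recall for these children, up to several weeks, so recall length still depends somewhat on how long the child was ill; the discharge summary helps to check it.
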